##### Secondary outcomes

The secondary outcomes of this clinical trial are changes in weight, BMI and waist circumferences (WC).

##### Procedure

After obtaining the informed consent, both groups will be visited at the clinical research center twice: at baseline, and after 10 weeks. Subjects will be interviewed regarding their socio-demographic background at baseline. At each visit, anthropometric indices (weight, height and waist circumference) will be measured, fasting blood sample will be collected and a 24-h food recall and international physical activity questionnaire (IPAQ) will be obtained.

Height will be measured using the SECA stadiometer to the nearest 0.1 cm and weight will be measured using a SECA electronic scale to the nearest 0.1 kg. Waist circumference will be measured midway between the lowest rib and the iliac crest using a non-stretchable measuring tape to the nearest 0.1 kg. BMI will be calculated as weight (kg) divided by height squared (m^2^). Venous blood sample (10 ml) will be drawn after 12-h overnight fasting by trained nurses in seated position to measure biochemical markers. Then blood samples will be centrifuged at 3000 rpm for 10 min at 4 °C to obtain the serum and plasma and will be stored at −80 °C until biochemical analyses. Lipid profiles (TC, HDL, LDL, TG) and glucose level will bemeasured by the enzymatic colorimetric method using kits. Serum insulin will be measured using enzyme-linked immunosorbent assay (ELISA) kit. Insulin sensitivity and insulin resistance will be determined using the QUICKI and HOMA-IR equation, respectively.$$ \mathrm{QUICK}=1\kern0.5em /\kern0.5em \left(\log \left(\mathrm{fasting}\kern0.5em \mathrm{insulin}\ \upmu \mathrm{U}/\mathrm{ml}\right)\kern0.5em +\kern0.5em \log\ \left(\mathrm{fasting}\  \mathrm{glucose}\ \mathrm{mg}/\mathrm{dl}\right)\right) $$$$ \mathrm{HOMA}\hbox{-} \mathrm{IR}=\kern0.5em \left(\mathrm{FPI}\left(\mathrm{mU}/\mathrm{l}\right)\kern0.5em \times \kern0.5em \mathrm{FPG}\kern0.5em \left(\mathrm{mmol}/\mathrm{l}\right)\right)/22.5 $$

Serum TAC [28] and level of SOD and GPx in red blood cells will be measured by spectrophotometric methods using kits. Serum irisin and SIRT1 will be measured using ELISA kits.

##### Assessment of dietary intake

To assess participants’ dietary intake, a 24-h food recall will be collected 3 times during the study (at baseline, middle and end of study). Patients will complete food descriptions including food and drinks (brand names), food preparation (ingredients) in detail as much as possible in the last day. Pictures of food commonly consumed in Iran, together with a set of common household measurement tools (glass, cup, soup bowls, plates, teaspoon and tablespoon) will be provided to assist subjects in estimating the portion sizes of the food. Dietary intake will be analysed with Nutritionist version 4.

##### Assessment of physical activity levels

IPAQ will be applied to assess the physical activity level of participants [29]. The IPAQ form comprises walking, moderate-intensity and vigorous-intensity activity and will be expressed as metabolic equivalents per minute (MET-min) per week. The levels of physical activity will be categorized into low, moderate and high, based on the IPAQ criteria.

##### Statistical analysis

All statistical analyses will be performed using SPSS version 21 (SPSS Inc., Chicago, USA). Data will be expressed as mean ± SD for continuous variables and percentage for non-continuous variables. Normality tests will be assessed through Shapiro-Wilk tests carried out on each parameter before analysis. All outcome variables will be assessed based on intention-to-treat and per protocol analysis. Missing data will be entered using “regression imputation” method. To compare the mean differences between the two groups, the independent *t*-test and Mann–Whitney will be used for normal and non-normal data respectively, considering the normality of data. A multivariate repeated-measures regression analysis will be used to assess time effects and time-by-treatment interactions effect on all outcome variables. A *p*-value of less than 0.05 will be considered as significant.

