### Inclusion and exclusion criteria

For the present study, T2DM patients, aged 30–60 years, with a diagnosis of T2DM for at least 2 years, HbA1C value greater than 7%, body mass index (BMI) between 25 and 35 kg/m^2^, who will be treated with a stabilized dose of oral anti-diabetic drugs and statins will be included in the study.

Patients will be excluded if: 1) they are pregnant or lactating; 2) have gastrointestinal disorders that interfere with the bowel function, severe hepatic, renal (dialysis), inflammatory and thyroid diseases; 3) being on insulin therapy or need insulin based on expert physician’s opinion 4) have diabetes complications including micro and macrovascular complications; 5) take warfarin, fibrates (PPAR- α ligand), TZD (PPAR- gammaligand) and anti-depressant agents; 6) adhering to a specific diet during the past 3 months; 7) have history of smoking or alcohol intake at least once a week in the past month; 8) receive (at least once a week) herbals, antioxidant, multivitamin/mineral supplements in the past 3 months; 9) they were unstable on the current dose of medications. Patients, who consume less than 90% of their intervention, will also be excluded.

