## Ethical considerations

This clinical trial will be conducted after approval by the Ethics Committee of Tehran University of Medical Sciencesand after obtaining informed consent from the participants. Whenever a person is unable to continue supplementation, he/she will be excluded from the study.

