## The limitations

One of the limitations of this study is the lack of cooperation of some patients who were replaced with other patients.

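### Intention-to-treat and per-protocol analyses are both planned for every outcome with neither ranked, and the exclusion and replacement statements leave room for a claim resting on the per-protocol set alone

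*Protocol article*

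**What the plan says.** In the protocol article, section Statistical analysis: "All outcome variables will be assessed based on intention-to-treat and per protocol analysis". The same paragraph gives one between-group comparison (t-test or Mann–Whitney), one missing-data method ("Missing data will be entered using “regression imputation” method") and one threshold: "A *p*-value of less than 0.05 will be considered as significant". No sentence makes one set primary, calls the other supportive, requires both to agree, or says how a disagreement is read.

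Three statements elsewhere affect who is analysed:

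- Inclusion and exclusion criteria: "Patients, who consume less than 90% of their intervention, will also be excluded".
- Ethical considerations: "Whenever a person is unable to continue supplementation, he/she will be excluded from the study".
- The limitations: "lack of cooperation of some patients who were replaced with other patients".

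The article gives no definition of the per-protocol set. The 90% intake figure used below is inferred from the first of these statements.

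**The concern.** This is a placebo-controlled trial testing for a difference, and only the comparison of all patients as randomised is protected by randomisation. A set chosen by capsule intake is formed afterwards. It can be biased if the reasons for low intake differ between cardamom and rusk capsules and are related to outcome.

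With both analyses planned for every outcome and no ranking, each outcome yields two results and the reader has no rule for choosing between them. One would normally presume that intention-to-treat prevails. Here that presumption is weak, because the exclusion and replacement statements, taken literally, remove patients from the study and not merely from a secondary set. A report built on the per-protocol result alone would be consistent with the article even if the randomised comparison were null. The problem exists for a single outcome, so controlling multiplicity over the outcomes would not remove it.

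**Working it through.** **Inputs from the article.** 40 per arm, two-sided 0.05, 80% power and a 20% drop-out allowance (Sample size). **Assumptions.** The share f of patients in the per-protocol set is 0.8, matching the drop-out allowance, with a range of 0.6 to 0.95. All randomised patients have an outcome for the intention-to-treat test.

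**The plan's own figure.** The 40 per arm cannot be reproduced, because the TAC difference and SD are not given. Back-solving n = 2(1.960 + 0.842)²/d²:

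- 32/(1 − 0.2) = 40 gives d = √(2/32) × 2.802 = 0.70.
- 33 × 1.2 = 39.6, rounded to 40, gives d = √(2/33) × 2.802 = 0.69.

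So d = 0.70 stands for the design effect. I add d = 0.45 as an assumed smaller effect.

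**Model, random subset.** The two test statistics are bivariate normal with correlation √f and means d/√(2/40) and d/√(2/(40f)). At f = 0.8 the correlation is 0.894. At d = 0.70 the means are 0.70/0.2236 = 3.13 and 0.70/0.25 = 2.80. Per-protocol-only positives equal P(either significant) − P(intention-to-treat significant). Intention-to-treat-only positives equal P(either) − P(per-protocol significant).

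| True d (f = 0.8) | ITT significant | PP significant | Either | PP only | ITT only | Disagree |
|---|---|---|---|---|---|---|
| 0 | 5.0% | 5.0% | 7.1% | 2.1% | 2.1% | 4.2% |
| 0.45 | 52.1% | 43.7% | 56.0% | 3.9% | 12.3% | 16.2% |
| 0.70 | 87.9% | 80.0% | 89.4% | 1.5% | 9.5% | 11.0% |

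Under no effect, the either-set rate runs from 6.0% (f = 0.95) to 8.0% (f = 0.6). A simulation with t-tests (40,000 runs, 40 per arm, f = 0.8) agrees: either-set 7.1% under the null, and per-protocol-only 2.1%, 4.0% and 1.6% at d = 0, 0.45 and 0.70.

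**If non-adherers gain nothing.** The table assumes the same effect in both sets. If the intention-to-treat effect is instead diluted to 0.8 × 0.70, intention-to-treat is significant in 70.7% and either set in 82.3%, so per-protocol-only positives are 82.3 − 70.7 = 11.6% (11.5% unrounded). An effect exists in this case, so these are not false positives. They concern adherers only.

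**Selection related to prognosis (assumed).** Let adherence correlate 0.5 with outcome and retain 80% of cardamom but 95% of placebo patients, with no true effect. The retained mean shifts by 0.5 × φ(z)/share, so the arms differ by 0.5 × (0.350 − 0.109) = 0.12 SD. Simulated, the per-protocol test alone rejects in about 8% and either set in about 10%. With the same correlation but 80% retained in both arms, the per-protocol test rejects in about 5% and either set in about 7%. The excess in the per-protocol test therefore comes from differential retention.

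**The case against.** The strongest reply is that planning both analyses is ordinary practice, and that ranking them is often left to a full protocol or SAP, which is not shown here. Naming intention-to-treat primary would add to the article's text without contradicting it. This has force against the claim that the sets are declared equal. A reader might infer that the plan grants equal standing, or that success in either set suffices. The article says neither: its 0.05 sentence is a general threshold, not a success criterion. The either-set rates above therefore describe a rule the text permits, not one it adopts.

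What remains is that the article is not silent on who is analysed. Its exclusion and replacement statements conflict with an intention-to-treat set on their face, and they weaken the default reading that would otherwise settle the matter.

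A second reply also stands. Disagreement rates of 16% and 11% might be read as the frequency of unwarranted claims. They are not: most of the disagreement is intention-to-treat-positive results lost to the lower power of a smaller set.

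A third is that no passage supports differential retention. The article gives a single overall 20% allowance, so the 10% figure shows what could happen and is not an estimate for this trial.

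Finally, the article does not say whether replacement occurred before or after randomisation. If it was before, that statement does not affect the analysis set.

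**Conclusion.** The point holds in a limited form. The article plans both analyses for all outcomes, does not say which decides, and contains statements that favour a set selected after randomisation. A per-protocol-only positive could therefore be presented as evidence of effectiveness.

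The inflation is modest: about 7% against 5% per outcome if either set may count and 80% are kept at random, with about 2% per-protocol-only positives under no effect and 2% to 4% under an effect equal in both sets. About 10% rests on assumed prognosis-related, differential retention. The documents do not support reading that as the expected error rate, nor reading the plan as an explicit either-set rule.

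The 13 primary outcomes at 0.05 each are a larger error-rate issue: if independent, 1 − 0.95¹³ = 0.49 with one set, and 1 − (1 − 0.0709)¹³ = 0.62 with either. The change is still worth making, because it costs little and settles a question that affects every outcome.

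**What to change.** In the Statistical analysis section, state:

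> The intention-to-treat analysis of all randomised patients, as allocated, is the primary analysis, and conclusions on efficacy rest on it alone. The per-protocol analysis (at least 90% intake) is supportive, is reported as an estimate with 95% confidence interval, and cannot by itself support a claim.

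That sentence is not enough alone. The statements in Inclusion and exclusion criteria, Ethical considerations and The limitations must be reconciled with it. Patients with low intake or who stop supplementation stay in the intention-to-treat set and are left out only of the per-protocol set. Any patient replaced after randomisation is still counted as randomised. This concerns who is analysed, not when supplementation stops.

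The cost is a few sentences, no additional patients, and no data beyond what an intention-to-treat analysis already calls for. The downside is that a positive per-protocol result can no longer carry a claim when the intention-to-treat result is null.

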### Sample size:

The sample size was calculated using the following equation:$$ n=\frac{{\left({Z}_{1-\alpha /2}+{Z}_{1-\beta}\right)}^2\left({S}_1^2+{S}_2^2\right)}{{\left({\mu}_1-{\mu}_2\right)}^2} $$

A total of 40 diabetic patients were calculated in each group (cardamom and placebo groups) based on a significant mean difference of TAC [24], with 95% confidence level, 80% power and additional drop-out rate of 20%.

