#### Study outcomes

##### Primary outcomes

The primary outcomes of this clinical trial are the changes in HbA1C, FBS, insulin, lipid profile (triglyceride, total cholesterol, HDL-cholesterol, LDL-cholesterol), oxidative stress biomarkers such as TAC, SOD, GPx, MDA, SIRT1 and irisin at the end of the study in comparison with the baseline values.

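### Regression imputation followed by ordinary tests distorts the intention-to-treat results: too many false positives if arm is an imputation predictor, a diluted effect if it is not

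*Protocol article*

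**What the plan says.** All of this is in the protocol article.

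- **Statistical analysis.** Every outcome is to be analysed by intention to treat and per protocol. On gaps in the data: "Missing data will be entered using “regression imputation” method". For the group comparison, "the independent *t*-test and Mann–Whitney will be used for normal and non-normal data respectively". A repeated-measures regression for time and time-by-treatment effects is added. On the threshold: "A *p*-value of less than 0.05 will be considered as significant". The section mentions no multiple imputation, no pooling and no variance correction.
- **Primary outcomes.** Thirteen variables are listed, each taken "at the end of the study in comparison with the baseline values", so the outcome scale is change from baseline.
- **Sample size.** Forty patients per group, from a two-means formula with "80% power and additional drop-out rate of 20" per cent.
- **Procedure.** Blood is drawn twice, at baseline and at 10 weeks.
- **Statements that bear on how much is imputed.** Inclusion and exclusion criteria removes patients who take under 90% of the capsules. Ethical considerations removes those who cannot continue. The limitations section says that some uncooperative patients were replaced.

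**The concern.** A regression prediction is not a measurement. If a missing week-10 value is replaced once by its predicted value and the file is then analysed as complete, the test counts 80 patients although fewer were measured. It ignores the uncertainty of the fitted line and, if no residual is added, the scatter around it.

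What follows depends on the predictors:

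- **Arm included.** Each filled value repeats the difference already seen between the arms. The estimate stays unbiased, but its standard error is too small and false positives exceed 5%.
- **Arm omitted.** Filled values are drawn towards a line common to both arms. The estimate is biased towards no effect.

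The method is stated for all outcomes, so the intention-to-treat p-values of all 13 primary outcomes are exposed to the extent that values are missing.

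**Working it through.** **Inputs from the document:** 40 per group; two-sided alpha 0.05; 80% power; 20% drop-out allowance; change score; t-test or Mann–Whitney.

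**Assumptions:** baseline-to-follow-up correlation 0 to 0.9; 8 of 40 week-10 values missing in each arm, completely at random; normal data unless noted.

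**1. The plan's own figure.** The article cites a source for the TAC difference and SDs but prints neither, so 40 can only be solved backwards. With n = 2(1.96 + 0.84)²/d², d = 0.71 gives 31.1, rounded up to 32, and 32/0.8 = 40. With d = 0.70, n = 32.04, rounded up to 33, and 33 × 1.2 = 39.6, rounded up to 40. The figure is consistent with the stated alpha, power and drop-out but cannot be verified. The allowance amounts to 0.20 × 80 = 16 values.

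**2. Closed form, arm included, no useful covariate.** Each gap is filled with its arm mean. The sum of squares comes from m = 32 values but is divided by n − 1 = 39, and the mean is credited with n = 40:

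reported SE / true SE = √[((m − 1)/(n − 1)) × (m/n)] = √[(31/39) × (32/40)] = √(0.795 × 0.80) ≈ 0.80.

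The nominal 5% test then runs at about 12%. This is the case in which baseline tells nothing about the value being tested.

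**3. Simulation, arm included, change score.** The week-10 value is predicted from baseline and arm with no residual added, and an ordinary t-test follows (20,000 runs per setting, 20% missing):

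| Correlation | 0 | 0.3 | 0.5 | 0.7 | 0.9 |
|---|---|---|---|---|---|
| Type I error, t-test | 7.9% | 9.0% | 9.6% | 10.3% | 11.2% |

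- Reported standard errors are 0.90 to 0.81 of the true ones, that is, 10% to 19% too small.
- One random residual added to each prediction hardly helps: 7.4% to 10.5%.
- With 10% missing, the error is 6.4% to 7.7%. With 5% missing, it is 5.6% to 6.3%.
- If the week-10 value itself were tested instead of the change, the pattern reverses: 11.9% at correlation 0, 9.7% at 0.5 and 5.9% at 0.9.

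**4. Mann–Whitney, same setting.** Type I error is about 8% at correlation 0 and about 15% at 0.9. At 0.3, 0.5 and 0.7 it is 9.5%, 10.9% and 12.6%. With log-normal data, where the plan would switch to this test, it is 10.7%, 12.4% and 14.6%.

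**5. Repeated-measures regression.** With two time points and every gap filled, its time-by-treatment test is equivalent to the change-score t-test, so step 3 applies to it as well.

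**6. Arm omitted.** Filled values carry no arm difference on average, so the expected estimate is 0.80 × 0.70 + 0.20 × 0 = 0.56 SD, an attenuation of 0.14/0.70 = 20%. Simulation gives 0.56. The t-test's type I error is 4.7% to 5.4%. At correlation 0.5, power is 0.76, against 0.78 from the observed cases alone, so the imputation gains nothing.

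**7. Remedies at 20% missing** (correlations 0, 0.5 and 0.7; 6,000 runs). Multiple imputation with 20 imputations and Rubin's rules gives type I error of 4.2% to 4.6%. Baseline-adjusted regression on the observed values gives 4.3% to 4.9%. Both are close to nominal.

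**The case against.** A reader might infer that the trial's 5% test will roughly double its error rate. The document does not support that without conditions, for four reasons.

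- The article names no predictors. If arm is left out there is no inflation at all. Dilution and inflation are alternatives and cannot both follow from the stated method. Naming the predictors is also something an article may leave to the full protocol or analysis plan.
- The words single and deterministic do not appear. A regression model can also drive multiple imputation.
- The 20% is a planning allowance for drop-out, not a forecast of imputed values. Applied as written, the exclusion and replacement statements could leave far fewer than 16 values to fill, and the inflation shrinks accordingly.
- The correlation is assumed. Figures for a baseline-adjusted test after filling would be higher still in some settings, but the plan names no such test, so they do not belong here.

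These objections limit the size of the problem and make it conditional; they do not remove it. The article does not merely leave the method open: it names one and follows it with ordinary tests. A single filling is the natural reading, and whichever way arm is treated, that reading gives a wrong answer. Reducing the number of imputed values by excluding patients would be at odds with the intention-to-treat analysis that the same article promises, so those statements must be reconciled in any case. The per-protocol analysis is a selected set and does not repair the intention-to-treat result.

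**Conclusion.** The sentence is wrong as written and should be changed, but the harm has to be stated conditionally. The figures rest on filling each gap once, data missing completely at random, a full 20% of week-10 values missing and imputed, and a correlation of 0 to 0.9.

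- **Arm in the imputation model:** about 8–11% instead of 5% for the change-score t-test, and about 8–15% for Mann–Whitney.
- **Arm omitted:** the error rate is sound, but the effect is understated by about a fifth.

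The document does not show which branch applies or how many values will be imputed, so neither an unconditional doubling nor both harms together can be claimed. With 5% missing, the inflation is small.

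**What to change.** Replace the imputation sentence with one of the following, chosen before the data are unblinded:

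- **(a) No imputation.** Analyse all observed values with a likelihood-based longitudinal model, or with a regression of the week-10 value on arm adjusted for baseline.
- **(b) Multiple imputation.** Use at least 20 imputations, with arm, baseline value, age and gender in the imputation model (age and gender are the stratification factors), combined by Rubin's rules.

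Rubin's rules combine estimates and standard errors, not Mann–Whitney p-values, so under (b) a skewed outcome needs an analysis that yields an estimate, for instance on a transformed scale. State also how patients who are excluded or replaced enter the intention-to-treat set, so that the number of missing values is defined. A sensitivity analysis that imputes from the placebo distribution is optional; this error does not require it.

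The cost is a change of wording and a little programming, with no effect on recruitment, visits or treatment. Intervals will be slightly wider, because they will reflect the data actually measured.

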### Randomization

Participants will be randomly allocated into two groups: cardamom and placebo groups and will be followed-up for 10 weeks. Randomizations will be conducted by an assistant using permuted block randomization method and stratified randomization will be used to match participants based on age and gender distribution. The intervention allocation will be blinded for both investigators and participants.

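### The planned between-group test is valid but inefficient: it uses neither the baseline value nor the age and gender strata as covariates, and with two visits the repeated-measures model as described adds nothing to it

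*Protocol article*

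**What the plan says.** All references are to the protocol article.

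- **Primary outcomes** defines thirteen laboratory variables as changes, taken "at the end of the study in comparison with the baseline values".
- **Statistical analysis** names the between-group comparison: an independent t-test for normal data, otherwise Mann–Whitney ("Mann–Whitney will be used for normal and non-normal data respectively, considering the normality of data"). It names no covariate. It adds a second model: "A multivariate repeated-measures regression analysis will be used to assess time effects and time-by-treatment interactions effect on all outcome variables". It lists no baseline covariate, no age or gender term, and no constraint on the baseline means for that model.
- **Procedure** fixes the measurement times: "both groups will be visited at the clinical research center twice: at baseline, and after 10 weeks". At each visit "anthropometric indices (weight, height and waist circumference) will be measured, fasting blood sample will be collected", so the baseline values of the outcomes are in hand.
- **Randomization** uses permuted blocks, and "stratified randomization will be used to match participants based on age and gender distribution".
- **Sample size** gives 40 per group for a difference in total antioxidant capacity (TAC), with two-sided 5% significance, 80% power and 20% drop-out. It states neither the difference nor the SDs.

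**The concern.** A change score subtracts the whole baseline value. With equal SDs at both visits, the best linear prediction of the week-10 value uses only the fraction rho of the baseline deviation. Subtracting all of it therefore adds noise whenever rho is below 1. ANCOVA estimates the fraction from the data and has the smaller variance.

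The second model looks as if it might recover this, but with only two outcome visits its interaction term compares the mean changes again.

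Randomisation is stratified by two factors that then disappear from the analysis. Stratifying reduces the true variance of the treatment contrast if the factors predict the analysed quantity. An analysis that leaves them out does not credit that reduction.

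At stake is power in a small trial. It is sized on TAC alone, so power for the other twelve primary variables is unstated.

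**Working it through.** **Inputs.** From the article: 40 per arm, 20% drop-out, two-sided alpha 0.05, 80% power, two visits, outcomes as changes, strata by age and gender. Not in the article, so assumed over a range: the baseline-to-week-10 correlation rho (0.3 to 0.9), equal SDs at the two visits, and the share of variance explained by age and gender (5% to 20%).

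**1. The plan's own sample size.** It cannot be reproduced forward, because the TAC difference and SDs are not given. Back-solved:
- Evaluable per arm: 40 × (1 − 0.20) = 32.
- Implied standardised difference: (1.960 + 0.842) × √(2/32) = 2.802 × 0.25 = 0.700.
- If drop-out was instead added as 33 × 1.20 = 39.6, rounded up to 40, the difference is 2.802 × √(2/33) = 0.690.

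I use 32 per arm and 0.70, read as a change-score SD. With the non-central t distribution in place of the normal approximation, power of the planned t-test is 78.7%.

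**2. Does the repeated-measures model help?** With two time points, complete data, no covariates and unconstrained baseline means, the time-by-treatment F equals the square of the change-score t. On one simulated data set of 32 per arm, both were 12.30, with p = 0.00085 for both.

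**3. Variance ratio.** With outcome variance s² at each visit:
- Change score: 2s²(1 − rho)
- ANCOVA: s²(1 − rho²)
- Ratio: (1 + rho)/2

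The standardised effect becomes 0.70/√ratio. Power at 32 per arm:

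| rho | ratio | extra patients the change score needs | effect under ANCOVA | power, change score | power, ANCOVA |
|---|---|---|---|---|---|
| 0.3 | 0.65 | 54% | 0.868 | 79% | 93% |
| 0.5 | 0.75 | 33% | 0.808 | 79% | 89% |
| 0.7 | 0.85 | 18% | 0.759 | 79% | 85% |
| 0.8 | 0.90 | 11% | 0.738 | 79% | 83% |
| 0.9 | 0.95 | 5% | 0.718 | 79% | 81% |

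Spending one degree of freedom on baseline and three on strata (four cells, an assumption because the age bands are not given) lowers these powers by less than 0.1 percentage point.

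**4. Chance imbalance.** The baseline difference between arms has standard error √(2/32) = 0.25 SD. A difference of that size shifts the change-score contrast by (1 − rho) × 0.25 outcome SD: 0.175 at rho 0.3, 0.125 at 0.5 and 0.025 at 0.9. Averaged over all randomisations the shift is zero.

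**5. Strata.** Let R² be the share of the variance of the *change* explained by age and gender. With balanced strata, the true size of the unadjusted test is about 2 × [1 − Φ(1.96/√(1 − R²))]:
- R² = 0.05: 4.4%
- R² = 0.10: 3.9%
- R² = 0.20: 2.8% (2.9% when simulated at 32 per arm)

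If age and gender shift only the *level*, equally at both visits, they subtract out of the change. Simulated size is then about 5%, even when they explain 10% to 20% of the level variance.

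**The case against.** **The test is valid.** This stands. Under randomisation the change-score t-test is unbiased and its type I error is not inflated. A reader might infer from step 4 that the planned estimate is biased. It is not: the shift is conditional on the imbalance that happens to occur.

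**The strata are harmless.** This stands in part. A reader might infer that leaving them out by itself brings the test size down to 3% or 4%. That requires age and gender to predict the 10-week change. Nothing in the article shows this, and eligibility limits age to 30–60 years.

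**The gain may be small.** This also stands in part. The primary outcomes include HbA1c and lipids in patients on stable medication, so high correlations cannot be excluded. At rho 0.9 the gain is about two percentage points of power. The formula also needs equal SDs, and the article does not say whether the TAC difference behind the sample size was a change or a final value.

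**Adjustment may be set out in a fuller plan.** The article does not rule this out, and the terms of the repeated-measures model may not be listed in full. However, the article does not leave the between-group method open: it names the tests. The point concerns that stated choice and how it fits the stated design. The equivalence in step 2 is claimed only for the model as described.

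**ANCOVA does not replace Mann–Whitney for skewed data.** This is correct, and the fix has to cover it.

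**Conclusion.** The point holds as one of efficiency and of fit between design and analysis. The named test discards baseline information that is already collected and omits the factors used to stratify, and the second model as described does not make up for either.

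The size depends on a correlation that the article does not give. Over rho from 0.3 to 0.9, power rises from 79% to between 93% and 81%, a gain of about 14 down to 2 percentage points. This rests on equal SDs at both visits, 32 evaluable patients per arm, and a back-solved effect of 0.70 change-score SD. The power figures apply to the t-test branch; none was calculated for Mann–Whitney.

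The loss from ignoring the strata is conditional: a test size of about 4.4% to 2.9% if age and gender explain 5% to 20% of the variance of the change, and about 5% if they affect only the level. The documents do not support a claim that the planned analysis is invalid, or that it is biased on average.

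**What to change.** Make the primary between-group analysis of each outcome an ANCOVA of the week-10 value on treatment, the baseline value of that outcome, and the age and gender stratification factors. Report the adjusted mean difference with its 95% confidence interval. With baseline in the model, using the change as response gives the same treatment estimate, so the outcome definition need not alter.

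For clearly skewed outcomes, state in advance what takes the place of Mann–Whitney: ANCOVA on the log scale, or a rank-based or robust ANCOVA. Keep the unadjusted t-test and Mann–Whitney as supportive analyses.

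The cost is wording and a few degrees of freedom. The exact number depends on how age is banded, which the article does not state. No new data are needed, because baseline values, age and gender are already required by the design.
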